### 1.4 Laboratory

Not applicable.

### 1.5 Monitoring institution

Please refer to section 1.1.

### 1.6 Data Safety Monitoring Committee (DSMC)

As the trials involves only minimal risks, is conducted with marketed and CE certified medical products, and is of only short duration, it is deemed not necessary to establish a DSMC.

## **2. ETHICAL AND REGULATORY ASPECTS**

The decision of the CEC and Swissmedic/foreign competent authority concerning the conduct of the study will be made in writing to the Sponsor-Investigator before commencement of this study. The clinical study can only begin once approval from all required authorities has been received. Any additional requirements imposed by the authorities shall be implemented. The clinical study will only begin after written approval of the CEC has been received.

### **2.1 Study registration**

The study protocol has been pre-registered on the Swiss Federal Complementary Database ([www.kofam.ch](http://www.kofam.ch), SNCTP000000873) and will be completed when CEC approval is given. Additionally, the trial has been registered at [www.clinicaltrials.gov](http://www.clinicaltrials.gov) (NCT02304120) and the study protocol will be submitted for publication in suitable peer-reviewed journals (e.g. BMC trials).

### **2.2 Categorisation of study (KlinV, Art. 19, 20, App 3, 1.1)**

The clinical trial and observational study corresponds to the Category A, as the product is authorised in Switzerland and the application is done according to the specific information.

### **2.3 Competent Ethics Committee (CEC)**

The responsible investigator (PL) will ensure that approval from CEC (EKNZ) is sought for the clinical study.

The PL is also responsible to uphold a weekly progress report that tracks number of:

- Screened patients
- Contacted participants
- Invited participants
- Recruited participants
- Drop-outs
- Measurement events
- Changes in research activity (setup, amendments)
- Unanticipated problems involving risks to humans
- Planned or premature study end

Also, a final study report will be submitted to the CEC after completion of the investigations. No changes will be made to the protocol without prior Sponsor and CEC approval, except where necessary to eliminate apparent immediate hazards to study participants.

Premature study end or interruption of the study will be reported within 15 days. The regular end of the study will be reported to the CEC within 90 days, the final study report shall be submitted within one year after study end. Amendments are reported according to chapter 2.10.

### **2.4 Competent Authorities (CA)**

Not applicable. There are no other authorities involved in this study.

### **2.5 Ethical Conduct of the Study**

The study will be carried out in accordance to the protocol and with principles enunciated in the current version of the Declaration of Helsinki, the guidelines of Good Clinical Practice (GCP) issued by ICH and the European Directive on medical devices 93/42/EEC and the ISO Norm 14155 and ISO 14971, the Swiss Law and Swiss regulatory authority's requirements. The CEC and regulatory authorities will receive annual safety and interim reports and be informed about study stop/end in agreement with local requirements.

## **2.6 Declaration of interest**

The PL is employed by the participating clinic (Reha Rheinfelden). The project is also financially supported by the ETH Zurich (Institute for Human Movement Science) for material and travel expenses. The steering committee declares there is no conflict of interest, whether intellectually or financially. There is no financial dependence from the developer of the therapeutic device; the company is not involved in the study initiation, planning, conducting, or data analysis and interpretation.

## **2.7 Patient Information and Informed Consent**

The investigators will explain to each participant the nature of the study, its purpose, the procedures involved, the expected duration, the potential risks and benefits and any discomfort it may entail. Each participant will be informed that the participation in the study is voluntary and that he/she may withdraw from the study at any time and that withdrawal of consent will not affect his/her subsequent medical assistance and treatment.

The participants of the intervention trial will also be informed that allocation to either treatment group will be based on randomisation and cannot be influenced. He or she must also know that if the baseline measurements are contraindicated to the treatment, exclusion of the intervention study may be possible after the second measurement event ( $T_0$ ), i.e. prior to begin of the intervention.

The participant will be informed that his/her medical records may be examined by authorised individuals other than their treating therapist.

All participants for the study will be provided a participant information sheet and a consent form describing the study and providing sufficient information for participant to make an informed decision about their participation in the study. The participants will have at least 24 hours to decide whether to participate or not.

The patient information sheet and the consent form will be submitted to the CEC and to the competent authority (as applicable) to be reviewed and approved. The formal consent of a participant, using the approved consent form, must be obtained before the participant is referred to any study procedure.

The participant will read and consider the statement before signing and dating the informed consent form, and will be given a copy of the signed document. The consent form will also be signed and dated by the investigator and it will be retained as part of the study records.

The participants of the study will not be compensated financially for their participation, but expenses will be reimbursed with CHF 10.00 per visit. Additionally, three entries to a local Spa-centre and one wellness massage will be raffled among all participants.

## **2.8 Participant privacy and confidentiality**

The investigator affirms and upholds the principle of the participant's right to privacy and that they shall comply with applicable privacy laws. Especially, anonymity of the participants shall be guaranteed when presenting the data at scientific meetings or article publications in scientific journals.

Individual subject medical information obtained as a result of this study is considered confidential and disclosure to third parties is prohibited. Subject confidentiality will be further ensured by utilising subject identification code numbers to correspond to treatment data in the computer files.

For data verification purposes, authorised by representatives of the Sponsor-Investigator, members of the ethics committee may require direct access to parts of the medical records relevant to the study, including participants' medical history.

## **2.9 Early termination of the study**

The Sponsor-Investigator may terminate the study prematurely according to certain circumstances, for example:

- ethical concerns,
- insufficient participant recruitment,
- when the safety of the participants is doubtful or at risk, respectively,
- alterations in accepted clinical practice that make the continuation of a clinical trial unwise,
- early evidence of benefit or harm of the experimental intervention.

## **2.10 Protocol amendments**

Only the PL can make amendments to the protocol but may designate technical assistants or study nurses to report changes to the CEC. The steering committee will be in continuous contact with the PL to suggest changes to the procedures, if necessary (e.g. eligibility criteria).

Substantial amendments are only implemented after approval of the CEC.

Under emergency circumstances, deviations from the protocol to protect the rights, safety and well-being of human subjects may proceed without prior approval of the sponsor and the CEC. Such deviations shall be documented and reported to the sponsor and the CEC as soon as possible.

All Non-substantial amendments are communicated to the CEC within the Annual Safety Report (ASR).

### 3. BACKGROUND AND RATIONALE

#### 3.1 Background and Rationale

In 2006, the European Cooperation in Science and Technology working group B13 (COST B13) published guidelines for chronic low back pain (CLBP) treatment [1]. The report estimates the lifetime prevalence to experience a first ever episode of low-back pain (LBP) at 84%. The State Secretariat for Economic Affairs (SECO) in Switzerland has released corresponding numbers in the context of preventive measures for occupational settings. According to the author, 18 % of all employees in Switzerland have reported some form of work related back pain accounting for 26 % of occupational absence with corresponding socio-economic consequences [2]. Although the bulk of the direct costs have been attributed to care by medical physicians and non-physicians [3], it is the indirect costs through absenteeism and social isolation that cause more than 80% of health costs. Hence, research promoting return to normal activity and prevention of chronicity of pain remains of great importance.

Where pain persists for more than 12 weeks and cannot be attributed to a recognisable, known specific pathology, the diagnosis is often chronic non-specific low back (CNLBP, ICD 54.5). This is the case in 80% of all pain patients referred to physiotherapy [1, 4]. Consequently there has been extensive research activity on the topic of CNLBP significantly contributing to the understanding of pain [5].

A proposed model describes the lack of variability as a possible cause for posture related stress to the musculoskeletal system [6-9]. In modern society accurate responses to dynamic movements are becoming ever more neglected. Repetitive tasks seem to dominate most of our activities. It has been well established that occupations requiring prolonged periods of static standing are associated with development of musculoskeletal disorders including LBP [10-12]. Long-term monotonous afferent input is believed to impair the sensorimotor system. Circuits regulating the appropriate amount of symmetric muscle force, needed to adapt the correct posture in any given situations, are thought to be disturbed [2, 8, 9, 13, 14]. If not restored, this constant malfunctioning of muscular control and regulation of dynamic movement may lead to inappropriate muscular activity [2, 14, 15] and is thought to contribute to taut muscles, imbalanced muscle activation, poor posture, and ultimately to musculoskeletal pain in lumbar regions.

Consequently, neuromuscular rehabilitation techniques addressing sensory deficiencies have emerged in recent years and have received increasing therapeutic attention [8, 9, 15-17]. These techniques could broadly be summarised as sensorimotor methods aiming at increased proprioceptive input to improve motor response to changing environments [15, 16]. It is believed that sensorimotor training (SMT) increases afferent proprioceptive stimulation of the segmental coordination through coupled anticipatory feed forward tasks and supervised postural response. This might lead to improved quality of postural control, which in turn may ultimately alleviate postural specific musculoskeletal pain.

There has been some doubt on whether such SMT can actually improve proprioceptive acuity in a functional way at all. In a recent review, Ashton-Miller et al. outlined a row of concerns (e.g. lack of neurophysiological evidence) about the validity of current proprioceptive exercises [18]. Although many therapists and clinicians report successful treatment cases, the exact effect and validity of sensorimotor interventions is still discussed controversially [18, 19]. Thus, the European Guidelines on the management of CNLBP do not include recommendations for SMT [1].

To assess the validity of these claims there is a need for outcomes that are capable of measuring postural motor control outcomes reliably and accurately in relation to pain and proprioception. Questionnaires for pain assessment are limited to self-reported indication of pain level which is a subjective measure. Functional assessment of postural control is also limited to clinical observation or outcomes that may be related to but not caused by motor control. Quantitative assessments e.g. COP, may be an objective and reliable tool for postural control assessment, but fails to describe the segmental coordination and ignores the individual variability inherent to human movement. Human posture requires complex mechanisms to perform the simplest of movements. Changing only one of the incoming control parameters leads to adaptation on all segments of the body, albeit not always detectable. This complexity is not captured with linear methods (e.g. mean and standard deviation of COP) [20, 21]. As Harbourne et al. point out, redundancy cannot be neglected when assessing the

quality of a task, as it is redundancy that allows the countless options humans have to react to varying perturbations [21].

The study has two interrelated aims. First, an experimental measurement setup is proposed that allows quantitative nonlinear analysis of COP and joint configuration during a dynamic postural task. The relationship of the proposed outcome with cervical proprioception is analysed and compared to healthy controls. Second, the efficacy of added proprioceptive training in conventional physiotherapy is assessed using the proposed parameters as secondary outcomes.

### **3.2 Investigational Product (treatment, device) and Indication**

There is a wide variety of ways how SMT can be performed. For this study, proprioceptive postural training (PPT) will be applied using the neuro-orthopaedic therapy device Posturomed®. The Posturomed consists of a labile platform, with adjustable damped swaying behaviour. Media-lateral and antero-posterior sway are increased when the two brakes, one at the front and one at the back, are released. This gives it three specific configurations with increasing levels of instability. The Posturomed® is used for therapy, but has also been used for assessment of postural [22]. In contrast to most proprioceptive training devices, the exercise plan for PPT is clearly defined, quickly explained to the patient and easily understood.

PPT is indicated for postural specific back pain, functional instability of weight-bearing joints (e.g. knee- or ankle instability), hypermobility, and other postural deficiencies. PPT is never applied as a stand-alone therapy but always embedded in multimodal therapy.

### **3.3 Preclinical Evidence**

Not applicable (marketed device).

### **3.4 Clinical Evidence to Date**

PPT will be performed using the neuro-orthopaedic therapeutic device Posturomed®. It was marketed in 1993 by a developer of orthopaedic chairs, Haider Bioswing, in collaboration with specialists from physical rehabilitation of pain [9]. It has been used as postural measure balance in a row of intervention studies after its physical characterisation and discriminant validity was confirmed [22, 23]. Combined with a non-contact path measuring system the therapeutic device is deemed to be suitable for characterizing balance abilities in an upright one-legged stance. Low variability of oscillation frequency suggests mechanically caused sway whereas the extent and duration of the oscillation is believed to be caused by the neuromuscular regulation of the subject. Hence, the Posturomed® can be combined with an accelerometer to quantify balance [22, 23].

In an unpublished thesis by Ganz et al. [24], postural control was significantly improved and reduced pain perception and functional impairment were reported. However, co-interventions were not controlled and group allocation was not randomised. Together with the small sample size applied, it is not possible to make any conclusive remarks on the clinical evidence for sensorimotor Training (SMT) effectiveness. Also, after conducting a systematic review on the topic of general SMT in pain rehabilitation [25], it was shown that no high-quality studies exist and that there is inconsistent evidence on the benefits of SMT.

### **3.5 Dose Rationale**

In a systematic review by [name] et al. [25] it was shown that no recommendations for dose selection for SMT implementation are available. Dose, frequency, and duration of SMT are still very much disputed, as sensory adaptation cannot be separated from motor learning. Dose selection for the current study is based on instructions of the usage of the medical device and on training principles in general.

### **3.6 Explanation for choice of comparator (or placebo)**

Low intensity endurance training (LIT) does not provide a specific treatment effect to the sensorimotor system but can improve the global perception of well-being. Although no cardiovascular response is expected at these low intensities, LIT can help to gradually increase the level of activity and participation and is therefore recommended as part of CNLBP treatments [4]. Moreover, LIT is easily standardised and monitored throughout the trial duration.

### **3.7 Risks/Benefits**

The exercises on the labile platform are rated as “absolutely safe” by the developer. Ever since the therapy has been implemented (1993), no adverse events have been reported during or after training on the device. The labile surface may trigger some fear of falling, but the railings that surround the device allow control of stability at any time. Nevertheless, it is not recommended to use the device during acute phases of intense pain or inflammation of weight bearing joints (e.g. knee or hip joints). Also, severe vestibular deficits or M. Menière may also lead to inability to stand stable and securely on the platform. To mitigate these risks, eligibility criteria will exclude participants with any risk-bearing contra-indications.

Although not confirmed systematically, the benefits expected outweigh the minimal risks by far. It is expected that an overall improvement of balance and postural control improves reactivity and reduces risk of falling in daily activity. Specific improvement of inter-vertebral musculature and improvement of the fine-tuned control of posture is believed to relax tensed poly-segmental muscles and decrease long-term strains and pain.

Patients that are enrolled into the study are covered by indemnity for non-negligent harm associated with the protocol through the clinic's own insurance (National Suisse, police-nr: 40.025.077). This will cover compensation or damages whether awarded voluntarily by the Sponsor, or by claims pursued through the courts. Incidences judged to arise from negligence (including those due to major protocol violations) will not be covered by study insurance policies.

If patients feel they benefited from the additional PPT therapy, additional training sessions can be organised for the patient. However, this will be outside of the study and will require either a new referral from the treating physician or the costs must be beard by the patient him- or herself.

Irrespective of treatment success, the study shall produce new insight into the understanding of the mechanisms behind human postural control and its relation to musculoskeletal pain.

### **3.8 Justification of choice of study population**

To study the effects of proprioceptive training, a population of chronic non-specific low back pain patients will be invited. As described above (Background and Rationale), the sensorimotor control is believed to be reduced in chronic low back pain. Hence it makes sense to test motor control and the efficacy of a sensorimotor training program with the suggested study population.

## **4. STUDY OBJECTIVES**

The overall objective of the study is to evaluate the effectiveness of a widely used but poorly investigated treatment method for non-specific low back pain rehabilitation. Secondary aims are to propose a measurement setup for dynamic postural control assessment and to provide insight into associations of postural deficiencies with proprioceptive accuracy and pain.

The three main research questions are:

1. Does a 5-week sensorimotor training intervention improve musculoskeletal pain and postural control?
2. Do patients with CNLBP present with poorer postural control and cervical proprioception than healthy controls?
3. Is there a relationship between cervical proprioception and postural control?

### **4.1 Overall Objective**

The purpose of this study is to evaluate the relationship between low back pain, postural control and cervical proprioception. Furthermore it will be shown whether additional sensorimotor training can effectively improve rehabilitation outcomes in patients with CNLBP.

### **4.2 Primary Objective**

The study seeks primarily to determine the effect of SMT on pain and functional status when added to conventional physiotherapy compared to usual treatment of patients with CNLBP.

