| Background and Rationale:                       | Sensorimotor training (SMT) is popularly applied as preventive or rehabilitative exercise method in various sports and rehabilitation settings, especially when postural control, linked to proprioception, is suspected to be deficient. Its effect, however, on pain and function is only poorly evaluated.                                                                                                                                                                                                                                                                               |
| Objective(s):                                   | The projects has two main objectives:

 
1. Measure effects of a four- to five- week sensorimotor training intervention, compared to low intensity endurance training, on musculoskeletal pain, functional status, postural control, and proprioception in patients with chronic non-specific low back pain.
 
2. Evaluate the relationship between cervical proprioception, postural control, and chronic non-specific low back pain (CNLBP) compared to healthy controls.
 
                                                        |
| Outcome(s):                                     | Primary outcomes:
Pain & Functional status: Visual Analogue Scale (VAS) and Oswestry Disability Index (ODI)

Secondary outcomes:
Postural Control: Sway of base of support (BOS), centre of pressure of BOS, Centre of Mass, Angular variation of involved segments, Uncontrolled Manifold Index before and after 5-week intervention.

Proprioception: Joint Repositioning Error of cervical, lumbar, hip, knee and ankle joints (before versus after perturbation) and head repositioning sense (HRS) before and after 5-week intervention. |

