| Study Product / Intervention:   | 
SMT will be performed with the Posturomed®. The Posturomed is a neuro-orthopaedic therapy device used in rehabilitative and exercise settings to prevent muscular imbalance and promote restitution of functional stability. A 7-stage protocol exists and is instructed by exercise therapists. This particular form of SMT is henceforth termed Postural Proprioceptive Therapy (PPT). Recommendations for home exercise will be provided.
                                                                                                                                                                                                                                                                                                                                                                                                                                                                                                                                                                                                                                                                                                                                                                                                                                             |

|                                               |                                                                                                                                                                                                                                                                                                 |
|-----------------------------------------------|-------------------------------------------------------------------------------------------------------------------------------------------------------------------------------------------------------------------------------------------------------------------------------------------------|
| Control Intervention (if applicable):  | PPT will be compared to a sham intervention (low-intensity endurance training).                                                                                                                                                                                                                 |

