## 6. STUDY DESIGN

### 6.1 General study design and justification of design

The intended procedures and study stages are summarised in Table 1 and Figure 1. Patients will be recruited from the out-patient department of the study site (Reha Rheinfelden) and public advertisement. In a cross-sectional study, baseline (BL) values are recorded to assess and to identify expected discrepancies in postural behaviour in a group-wise comparison (healthy vs. patients with LBP). In a pilot randomised sham-controlled trial (RCT) with parallel groups and blinded assessors, the effects of added SMT to conventional therapy in comparison to added LIT will be evaluated on three additional measurement events. The primary endpoints are pain and function before ( $T_0$ ) and after 9 treatments during 5 weeks (twice a week). Short-term effects will be evaluated within a week after the last training session ( $T_1$ ). Long-term effects will be tested four weeks after the last training session ( $T_2$ ).

*Screening and pre-intervention assessments:* Potential participants will be informed (personal or by phone and email) of the study procedures, risks and expenses, and possible benefits (according to the patient information sheet approved by the competent ethical committee, CEC). After written and oral information, the patient will have one to three days to consider participation before giving informed consent. Once written consent is provided, a baseline measurement will take place 2 to 4 days prior to therapy commencement. For healthy participants there is no time constraint. An internal rheumatologist will confirm the diagnosis for patients who are not referred to the clinic by their treating physicians. The BL assessment will reveal whether all eligibility criteria are fulfilled and whether trial participation is granted. Patients will also be asked to give a second oral consent to further participate in the trial. Once included and randomised for treatment groups, all analysis will follow intention-to-treat principles (as-per-case analysis will also be conducted).  $T_0$  will be conducted immediately before first treatment to ensure a stable baseline (4 to 7 days after BL).

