*Interventions and follow-up assessments:* Patient allocation to either the sham- or the experimental PPT group will be block-randomised with a 1:1 allocation ratio. The sequence list will be guarded by the central pharmacy (central randomisation list). Before the first treatment begins, the treating therapist will call the pharmacy to learn the allocated group belonging to the patient's identification number. All patients will receive usual physiotherapy as deemed appropriate by the therapist for 30 minutes. Patients allocated to the CG will subsequently be instructed on how to use the treadmill, stationary bike, or cross-fit trainer at low intensity (Borg 6-9). Patients in EG will receive supervised instructions to use the therapy device (Posturomed®) correctly. For treatments 2 to 9, patients in both groups will not be supervised directly but a trained therapist will be nearby to oversee the compliance and correct execution of the exercise. The therapist will evaluate quality of the execution of exercises after the 3rd and 6th session to instruct increased difficulty if the patient already masters the task. Within one or two days after the 9th treatment, the second assessment ( $T_1$ ) of primary and secondary outcomes will be conducted by the PL or a technical assistant to record possible short-term effects. Finally, four weeks after the last treatment a follow-up measurement will assess long-term effects of the treatments. All measurement events (ME) are expected to take about 60 minutes for all outcome assessments. Total therapy duration is 45 minutes (30 minutes therapy and 15 minutes experimental or sham intervention). The therapist will be blinded to the results of all primary and secondary outcomes. The assessor will remain blinded to group-allocation. For description of the sequence generation and randomisation procedures, please refer to section 6.2.

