*Limitations:* The study-protocol features some technical, methodological and physiological limitations that must be considered when interpreting the results. First, the physiological limitation concerns the indirect measure of proprioception which limits the interpretation regarding increased afferent input. Joint repositioning sense only tests one aspect of proprioception on a conscious level. Second, from a methodological point of view, it is not possible to blind the therapist or the patient to the intervention. This may influence the way patients respond to subjective outcomes and could potentially bias the results. Furthermore, in a clinical setting it is not possible to control all co-interventions as treatment must be adapted to the needs and indications of each patient. With multiple therapists at work standardisation of the experimental intervention is adamant. Third, the recording of non-active markers is always related to some inaccuracies. The measurement device records with a resolution that allows accuracy of about 3 mm. This may limit the detectability of the expected change in postural control.

A further methodological limitation is that both assessment for secondary outcomes and the experimental intervention involve the same device (Posturomed). However, the task for the assessment deviates substantially from the training task and no advantage is expected for EG group when performing the postural control task (described in section 9.2.2).

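### Section 4.2 sets SMT against usual treatment, but the trial randomises SMT against added endurance exercise, and calling that exercise a sham overstates the control

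*Protocol*

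**What the plan says.** Protocol 4.2 gives the primary objective as the effect of SMT on pain and functional status "when added to conventional physiotherapy compared to usual treatment of patients with CNLBP".

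Other parts of the protocol name a different comparator. Synopsis objective 1 is to measure the effects of a "sensorimotor training intervention, compared to low intensity endurance training, on musculoskeletal pain, functional status, postural control, and proprioception". Section 6.1 says that "the effects of added SMT to conventional therapy in comparison to added LIT will be evaluated".

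On what each arm receives, 6.1 states: "All patients will receive usual physiotherapy as deemed appropriate by the therapist for 30 minutes". The control group then does LIT and the experimental group trains on the Posturomed. Section 8.1.2 and the synopsis (Measurements and procedures) likewise place LIT on top of conventional therapy for every control patient. Allocation is 1:1 between these two groups.

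On the label, the synopsis (Control Intervention) says "PPT will be compared to a sham intervention (low-intensity endurance training)". Section 6.1 calls the trial sham-controlled and refers to a sham group. Section 3.6, which justifies the comparator, says that "LIT can help to gradually increase the level of activity and participation and is therefore recommended as part of CNLBP treatments" and that it may improve general well-being. The limitations paragraph of 6.1 says "it is not possible to blind the therapist or the patient to the intervention".

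**The concern.** The primary objective fixes which question the trial may claim to have answered. As written, 4.2 names a comparison for which there is no control group. If the result is reported under that objective, a null finding could be read as showing that SMT adds nothing to usual treatment, when the data would equally fit both exercise blocks helping to a similar degree.

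The sham label causes trouble in the other direction. A reader who meets *sham-controlled* will usually take it that the comparator has no relevant action of its own and that patient expectation is balanced between arms. Neither is secured here. The primary outcomes, VAS pain and ODI, are filled in by patients who know which training they received, so blinding the assessor does not protect them.

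**Working it through.** The stated objective contains no figure to reproduce. The check compares the stated contrast with the randomised one.

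**Step 1: what usual treatment means here.** Section 6.1 gives every patient 30 minutes of usual physiotherapy per session. Section 8.2.1 describes this as usual care under the patient's own treatment plan, unaffected by the study. LIT is not part of it; 6.1 and 8.1.2 add it afterwards.

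**Step 2: the arms.**

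| Source | Experimental arm | Comparator |
|---|---|---|
| 4.2 | physiotherapy + SMT | usual treatment |
| Synopsis objective 1 | SMT | LIT |
| 6.1 | conventional therapy + SMT | conventional therapy + LIT |
| 8.1.1 and 8.1.2 | conventional therapy + PPT | conventional therapy + LIT |

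Section 4.2 is the outlier.

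**Step 3: the two contrasts.** Let m(·) be the mean outcome (VAS or ODI) under a regimen and PT the usual physiotherapy.

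- Contrast in 4.2: A = m(PT+PPT) − m(PT)
- Randomised contrast: B = m(PT+PPT) − m(PT+LIT)
- Effect of LIT over physiotherapy alone: L = m(PT+LIT) − m(PT)

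Adding and subtracting m(PT) in B gives B = A − L. So B = A only if L = 0.

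**Step 4: can L be learned from the trial or the protocol?** Not from the trial, because no randomised patient receives PT alone. The control arm's change from T0 to T1 does not isolate L either, since it mixes physiotherapy, natural course and LIT. Not from the protocol, because 3.6 gives no effect of LIT on pain or ODI, and the sample-size section (11.2) states neither a difference nor a standard deviation for VAS or ODI. The gap between A and B is therefore unquantified, and any number put on it would be an assumption.

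**Step 5: does the sham label fit?**

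- *Inactivity.* Section 3.6 says LIT has no specific action on the sensorimotor system and is too light to provoke a cardiovascular response. That bears mainly on the postural and proprioceptive secondary outcomes. The primary outcomes (5.1, 9.2.1) are daily function and pain, and 3.6 credits LIT with possible gains in well-being, activity and participation. L = 0 on the primary outcomes is thus not shown.
- *Masking.* Patients are not blinded (6.1), and 6.2.3 confirms that the pain and function questionnaires are completed by the patients themselves.
- *Delivery.* Under 8.2.2 a therapist moves the patient through stages of difficulty, whereas under 8.2.3 the LIT intensity stays as first set. Equal therapist attention is therefore not evident.

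**The case against.** The strongest reply is that this is one loose sentence in an otherwise consistent plan. Much of that stands. Synopsis objective 1 and section 6.1 both name LIT, and the procedures follow them. A reader might infer that the whole protocol misstates its comparator, but the text does not support this. Section 4.1 asks only "whether additional sensorimotor training can effectively improve rehabilitation outcomes in patients with CNLBP" and names no comparator; nor does research question 1 in section 4. The primary hypotheses in 11.1 already compare the experimental with the control group. The explicit conflict is confined to 4.2.

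A second reply is that LIT was chosen because it lacks the specific sensorimotor ingredient, so *sham* is a reasonable shorthand, and that 6.1 openly warns that lack of blinding may bias subjective outcomes. The rationale and the disclosure are both there. It would also go too far to infer that the protocol concedes a LIT effect on pain or disability: 3.6 is hedged and mentions neither. What remains is that the label asserts a property the plan does not establish for its primary outcomes, and the caveat in 6.1 sits beside that label without correcting it.

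A third reply is that, since LIT is recommended care, *usual treatment* in 4.2 might be meant to include it. Sections 6.1 and 8.2.1 rule this out by treating LIT as a study addition to usual physiotherapy. If that reading were adopted, the sham label would be harder still to defend.

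**Conclusion.** The point holds for section 4.2 and for the sham wording. The stated primary contrast cannot be estimated from this design. The trial estimates PPT versus LIT, each on top of physiotherapy, and this differs from the 4.2 contrast by the unknown effect of LIT over physiotherapy alone. The conclusion rests only on the protocol's description of the two arms and needs no assumption about how large the LIT effect is.

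Two stronger readings should be resisted. One is that the design is at fault: an added-exercise comparator is a legitimate choice, and nothing in the protocol makes it invalid. The other is that a clinically relevant benefit would be hidden by some stated amount. The documents give no LIT effect from which such an amount could be derived, and they do not show that LIT has one.

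Randomisation, data collection and analysis are unaffected. What changes is the conclusion the trial may draw on its primary question. Even for a trial described as pilot and explorative, that is enough to require correction.

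**What to change.** - **4.2:** restate the primary objective as the effect on pain and functional status of PPT plus physiotherapy versus LIT plus physiotherapy, in line with synopsis objective 1 and 6.1.
- **Synopsis (Control Intervention) and 6.1:** replace *sham* and *sham-controlled* with *active exercise comparator, patients not blinded, assessor-blinded*. Section 6.1 already mentions blinded assessors, so only the sham terms and the patients' status need changing there.
- **Interpretation:** add a sentence, for example in the limitations of 6.1, that neither a null nor a positive result estimates the effect of adding SMT to physiotherapy alone.
- **Optional:** name the comparator in 4.1 and research question 1 for clarity. The hypotheses in 11.1 need no change.

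This is a wording amendment with no effect on procedures, sample size or analysis. Its cost is a narrower claim: the trial can speak to PPT against LIT, not to SMT against usual treatment.
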